## Abstract

**Background:**

Musculoskeletal disorders (MSKDs) are a leading cause of pain and disability, placing a substantial burden on health care systems. Optimizing resource use through innovative interventions is essential. Evidence from randomized controlled trials suggests that not all individuals with MSKDs require ongoing follow-up with a health care provider; for many, education alone is sufficient for symptom resolution. A stepped care model, which prioritizes patient education as a first-line intervention and reserves usual care for those with persistent symptoms, may enhance health care efficiency and reduce costs.

**Objective:**

The primary objective of this randomized controlled trial is to evaluate the effectiveness of a stepped care model compared to the 2 most common approaches for managing MSKDs: usual medical care and usual rehabilitation care. A secondary objective is to assess cost-effectiveness.

**Methods:**

This pragmatic, noninferiority, multiarm, parallel-group randomized controlled trial will enroll 369 adults with MSKDs, randomly assigned to one of three 12-week intervention groups: stepped care, usual medical care (physician-led), or usual rehabilitation care (physiotherapist-led). Participants in the stepped care group will first complete a 6-week education program. Those with persistent symptoms after 6 weeks will receive rehabilitation interventions, while participants whose symptoms have resolved will receive no further intervention. The primary outcome is functional limitations at 24 weeks. Secondary outcomes include pain severity, health-related quality of life, pain-related fear, and pain self-efficacy, assessed at baseline and at 6, 12, and 24 weeks. Linear mixed models will be used for group comparisons, and incremental cost-effectiveness analyses will evaluate cost-effectiveness. The ethics committee of the CIUSSS-CN approved the project (#2024-2982). Findings will be shared through clinical and community platforms, peer-reviewed publications, and conference presentations.

**Results:**

The Edu-First trial is funded by a project grant from the Canadian Institutes of Health Research (grant #495615). Recruitment began on January 31, 2025. As of September 2025, a total of 65 participants have been enrolled. Recruitment is expected to continue for up to 3 years, targeting approximately 10 new participants per month, and is anticipated to be completed by Winter 2028.

**Conclusions:**

We anticipate that the stepped care model will be noninferior to usual medical care and usual rehabilitation care in terms of treatment effectiveness. Furthermore, it is expected to be cost-effective by reducing reliance on expensive resources, such as provider consultations and medical investigations. By emphasizing education and self-management as the initial approach, the stepped care model may enhance access to care without compromising quality, while empowering patients to actively manage their condition. Findings from this study could inform systemic changes in MSKD care delivery, improving treatment accessibility and reducing the average cost per care episode.

**Trial Registration:**

ClinicalTrial.gov NCT06832852; https://clinicaltrials.gov/ct2/show/NCT06832852

**International Registered Report Identifier (IRRID):**

DERR1-10.2196/77574

## Introduction

Musculoskeletal disorders (MSKDs) have become a global epidemic, with their prevalence steadily rising over the past decades [1]. This trend is expected to persist due to aging populations and ongoing exposure to environmental and occupational risk factors [1,2]. MSKDs significantly impact individuals by limiting activities and restricting participation while also placing a heavy burden on society through work absenteeism, disability pensions, early retirement, and increasing demands for social support [3,4]. While some individuals experience short-term symptoms, others endure persistent or recurrent pain, leading to impaired daily functioning and substantial health care costs [5-7]. MSKDs are among the most common reasons for seeking primary care, with up to 20% of adults consulting their family physician for an MSKD-related issue annually [8]. Ensuring timely and appropriate care for individuals with MSKDs remains a challenge, even in countries with universal health care [9].

A major barrier to health care access for individuals with MSKDs is prolonged wait times [10-12]. In addition, significant gaps and disparities in access to publicly funded health care persist across several countries [11,13-15]. A systematic review reported significant declines in health-related quality of life and psychological well-being among those experiencing treatment delays [16]. Longer wait times have also been associated with increased health care use, delays, or restrictions in work participation [17]. To address these challenges, health care services must be redesigned to reduce wait times and promote more equitable access. A systematic review examining strategies to reduce waiting times in outpatient rehabilitation services for adults with MSKDs found that several service redesign approaches—such as referral management strategies and alternative models of care—effectively decreased waiting times while better meeting patients’ needs [18]. Given the negative consequences of prolonged delays, implementing efficient and effective strategies to improve timely access to care for individuals with MSKDs is essential.

In 2 randomized controlled trials, we demonstrated that not all patients with chronic MSKDs require close follow-up by a health care provider, as for a large proportion, patient education alone was sufficient to achieve significant improvement or even resolution of their condition [19,20]. As a first-line approach in primary care, patient education is cost-effective, widely accessible, and adaptable [11,21], and in some cases, it is as effective as usual care [22,23]. It can be delivered by various health care providers in multiple formats, including self-administered options, depending on the context and individual needs [24]. The primary goals of education are to improve patients’ understanding of their condition, dispel myths and misconceptions, promote healthy lifestyle choices, and optimize self-management [25-27]. A better understanding of the condition and its psychological factors enables individuals to manage their symptoms more effectively [28,29]. As health care costs rise, a stepped care model—where patient education and advice are offered first, with usual care provided only to those whose symptoms persist—could improve access to health care by reducing the number of visits with a health care provider without compromising quality of care.

The primary objective of this randomized controlled trial is to determine whether a stepped care model is as effective as the 2 most common care models—usual medical care (led by a family physician) and usual rehabilitation care (led by a physiotherapist)—in individuals with MSKDs at 24 weeks post allocation. The primary outcome will be functional limitations at 24 weeks. Secondary outcomes will include functional limitations at 6 and 12 weeks, as well as pain intensity, health-related quality of life, region-specific symptoms and functional limitations, pain-related fear, pain catastrophizing, pain self-efficacy, and satisfaction with care at 6, 12, and 24 weeks. The secondary objective is to investigate the cost-effectiveness of a stepped care model compared to usual medical care and usual rehabilitation care for managing MSKDs in Canadian adults over a 24-week period. We hypothesize that the stepped care model will be noninferior to usual medical care and usual rehabilitation care in terms of effectiveness. In addition, we expect health care costs to be significantly lower for the stepped care model due to a reduction in the use of costly resources, such as consultations with health care providers and medical investigations (eg, laboratory tests and medical imaging).

## Methods

### Study Design

A pragmatic, noninferiority, multiarm, parallel-group randomized controlled trial will be conducted in the Quebec City area, Canada, targeting individuals with 1of the 4 most common MSKDs encountered in primary care: low back pain, neck pain, rotator cuff–related shoulder pain, or anterior knee pain [30,31] (see Figure 1). This pragmatic trial will reflect real-world clinical practice, as participants will receive care in routine medical and rehabilitation settings [32-37]. The trial is registered at ClinicalTrials.gov (NCT06832852), and follows the multiarm extension of the Consolidated Standards of Reporting Trials (CONSORT) guidelines [38], as well as the Standard Protocol Items: Recommendations for Interventional Trials (SPIRIT) guidelines [39,40]. Interventions in each arm are described according to the Template for Intervention Description and Replication (TIDieR) checklist [41].

**Figure 1 figure1:**
[figure not shown]
Study flow diagram.

Participants will be recruited through a convenience sample using various channels, including social media platforms (Facebook, LinkedIn, and Instagram), electronic mailing lists of students, employees, and retirees at Université Laval, and advertisements in local newspapers. Interested individuals will be invited to contact the research team by email or phone. Initial eligibility screening will be conducted online using a web-based questionnaire through REDCap (Research Electronic Data Capture; Vanderbilt University) platform [42]. During this process, potential participants will receive information outlining the nature and objectives of the study. A follow-up phone interview with a team member will provide further eligibility screening and an opportunity to discuss the study details.

Individuals who meet the initial criteria will be asked to provide electronic informed consent, complete the primary and some secondary outcome measures using web-based patient-reported outcome measures within REDCap (see Figure 2), and attend an in-person meeting at the Center for Interdisciplinary Research in Rehabilitation and Social Integration (Cirris), a research center affiliated with Université Laval in Quebec City. During this meeting, an experienced physiotherapist will confirm eligibility using standardized screening questionnaires and, for certain diagnoses (eg, rotator cuff–related shoulder pain and anterior knee pain), additional physical tests. All screening questionnaires used throughout the recruitment process are provided in Multimedia Appendix 1.

**Figure 2 figure2:**
[figure not shown]
Standard Protocol Items: Recommendations for Interventional Trials (SPIRIT) diagram of enrolment, interventions, and assessments. BPI-SF: Brief Pain Inventory–Short Form; CoPaQ: Cost for Patients Questionnaire; CSI: Central Sensitization Inventory; HADS: Hospital Anxiety and Depression Scale; KOS-ADLS: Knee Outcome Survey Activities of Daily Living Scale; NDI: Neck Disability Index; ODI: modified Oswestry Disability Index; ÖMPQ: OREBRO musculoskeletal pain questionnaire; PASS: Patient Acceptable Symptom State; PCS: Pain Catastrophizing Scale; PSEQ: Pain Self-Efficacy Questionnaire; QuickDASH: shortened version of the Disabilities of the Arm, Shoulder, and Hand; TSK: Tampa Scale of Kinesiophobia.

During the in-person meeting, enrolled participants will also complete the baseline evaluation, which includes questionnaires on sociodemographic characteristics (including sex at birth and gender identity), medical history, symptom onset context, work restrictions, recovery expectations (participants’ expectations regarding the intervention’s potential effectiveness on their pain, work capacity, and ability to engage in leisure activities) [43], and treatment preferences (eg, preferred health care provider, desired duration and frequency of consultations) [44,45]. Finally, the remaining secondary outcome measures will be evaluated on-site using web-based patient-reported outcome measures in REDCap. Participants will then be randomly assigned to one of three 12-week intervention groups: stepped care, usual rehabilitation care, or usual medical care. Recovery expectations will be reassessed immediately after participants receive an explanation of their assigned intervention.

Primary and secondary outcome measures will be reassessed online using web-based patient-reported outcome measures in REDCap at 6, 12, and 24 weeks post allocation (see Figures 1 and 2).

### Population and Sample Size

Participants must be aged between 18 and 65 years, present with 1 of the 4 targeted MSKDs (low back pain, neck pain, rotator cuff–related shoulder pain, and anterior knee pain), and have experienced pain for at least 6 weeks. Potential participants will be excluded if they: (1) are unavailable for the 12-week intervention; (2) cannot understand or read French or English; (3) have a diagnosis of rheumatoid, inflammatory or neurodegenerative diseases; (4) have signs of upper (eg, bilateral paresthesia, hyperreflexia, or spasticity) or lower (eg, decreased sensation or strength in dermatomes and myotomes, hypotonia, or hyporeflexia) motor neuron lesions; (5) have received a corticosteroid injection or any other type of injection (eg, platelet-rich plasma, prolotherapy, and hyaluronic acid) in the past 3 months for their current condition; and (6) have cognitive impairments interfering with participation (mini—mental state examination administered if doubts arise; score must be ≥24) [46,47]. Participants who previously received conservative management will be eligible if at least 6 weeks have passed since their last intervention (including prescribed condition-specific exercises or medication). Specific inclusion and exclusion criteria for each MSKDs are the following.

#### Low Back Pain

Inclusion criteria are (1) nonspecific low back pain with or without radiation to the lower limbs, (2) minimum score of 15/100 on the modified Oswestry Disability Index (ODI; 1.5 times the minimally clinically important difference [48], to ensure participants have clinically significant symptoms). Nonspecific low back pain is defined as low back pain that cannot be attributed to a specific condition. Exclusion criteria are (1) low back pain related to specific conditions (eg, vertebral fracture, infections, and neuropathic pain, with a score of ≥4 on the DN4 [Douleur Neuropathique 4, a screening questionnaire used to identify neuropathic pain] questionnaire [49]) and (2) history of spine surgery.

#### Neck Pain

Inclusion criteria are (1) nonspecific neck pain with or without radiation to the upper limbs and (2) a minimum score of 21/100 on the Neck Disability Index (1.5 times the minimally clinically important difference [50]) to ensure participants have clinically significant symptoms). Exclusion criteria are (1) neck pain related to specific conditions (eg, vertebral fracture, infections, and neuropathic pain; ≥4 on the DN4 questionnaire [49]), (2) history of spine surgery, or (3) signs of upper or lower motor neuron lesions.

#### Rotator Cuff–Related Shoulder Pain

Inclusion criteria are (1) shoulder pain attributed to rotator cuff–related shoulder pain (pain over the deltoid or upper arm region, pain associated with arm movement [painful arc of movement], and familiar pain reproduced with loading or resisted testing during external rotation of the arm) [36,51], and (2) a minimum score of 15/100 on the shortened version of the Disabilities of the Arm, Shoulder, and Hand (QuickDASH; 1.5 times the minimally clinically important difference [52], to ensure participants have clinically significant symptoms). Exclusion criteria are (1) history of shoulder surgery, dislocation, or fracture; (2) presence of severe osteoarthritis, symptomatic acromioclavicular joint pathology, or adhesive capsulitis (defined as restriction of passive glenohumeral movement of at least 30% for two or more directions); and (3) full thickness rotator cuff tear, identified by imaging or clinical tests (lag signs and gross weakness) [53,54].

#### Anterior Knee Pain

Inclusion criteria are (1) anterior knee pain during walking, running or going up or down stairs, or during at least two activities among: kneeling, squatting, and resisted knee extension [55] and (2) maximum score of 79/100 on the Knee Outcome Survey Activities of Daily Living Scale (1.5 times the minimally clinically important difference [56], to ensure participants have clinically significant symptoms). Exclusion criteria are (1) history of knee surgery or patellar dislocation, and (2) pain believed to originate either from the meniscus [57] or any knee ligament based on clinical tests.

The primary objective is to assess the equivalence between the stepped care model and the 2 usual care models. With 123 participants per group, we will have 80% power to test the noninferiority of the stepped care model compared to usual rehabilitation care and usual medical care, using a noninferiority margin of 2.0 (out of 10) points on the primary outcome measure. This margin is based on the highest suggested minimally clinically important difference for the Pain Interference subscale of the Brief Pain Inventory—Short Form (BPI-SF) [58]. The sample size calculation assumes a true mean difference of 0 between groups, and an SD of 1.8 in the usual care groups [59], a 15% dropout rate at the 24-week follow-up [20,60-62], and a 1-sided alpha level of .025.

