
#### Primary Outcome: Functional limitations

The BPI-SF is an 11-item questionnaire comprising two subscales: the 4-item Pain Severity subscale and the 7-item Pain Interference subscale. It has been shown to be valid, reliable, and responsive for MSKDs [71-74]. The Pain Interference subscale, measured at the 24-week follow-up, will be the primary outcome measure, assessing the extent to which pain disrupts daily functioning [73,74]. Its minimally clinically important difference ranges from 1.3 to 2.0 out of 10 points [58].

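### The stated margin, SD, power and sample size do not agree: a 2.0-point margin with SD 1.8 needs about 16 per group for 80% power, not 123

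*Protocol article*

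**What the plan says.** The calculation is in the protocol article, Methods, Population and Sample Size, in the last paragraph (printed under the Anterior Knee Pain subheading). It claims: "With 123 participants per group, we will have 80% power to test the noninferiority of the stepped care model", against both usual care models, "using a noninferiority margin of 2.0 (out of 10) points on the primary outcome measure". The margin has a stated rationale: "This margin is based on the highest suggested minimally clinically important difference for the Pain Interference subscale". The section Primary Outcome: Functional limitations gives the range behind that choice: "Its minimally clinically important difference ranges from 1.3 to 2.0 out of 10 points".

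The remaining inputs follow in the same paragraph: "The sample size calculation assumes a true mean difference of 0 between groups, and an SD of 1.8 in the usual care groups", with 15% dropout at 24 weeks and a one-sided alpha of .025. The Abstract gives the matching total: "randomized controlled trial will enroll 369 adults with MSKDs", which is 3 × 123. The article states no other margin, and no multiplicity adjustment, clustering inflation or subgroup-based sizing.

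**The concern.** The paragraph lists every input that a two-group noninferiority calculation on means needs, so it can be checked directly. The margin is larger than one SD (2.0/1.8 = 1.11). With no assumed true difference, a distance of that size needs very few participants, so 123 per group at only 80% power cannot be right.

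The margin is the threshold for the primary conclusion. If the calculation rested on a shorter distance than the one printed, the printed margin may not be the one the trial was sized to test, and noninferiority would be easier to declare than the sample size suggests. If 2.0 is correct, the power is misreported and recruiting 369 people has no stated statistical justification.

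**Working it through.** **Inputs** (all from the sample-size paragraph): margin 2.0; true difference 0; SD 1.8, taken as common to the arms; one-sided alpha .025 (z = 1.95996); power 80% (z = 0.84162); dropout 15%. The two z values sum to 2.8016. Allocation is 1:1:1 (Randomization and Blinding).

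**1. The plan's own figure from its own inputs.**

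n per group = 2 × [(z for alpha + z for power) × SD / (margin − true difference)]²

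= 2 × (2.8016 × 1.8 / 2.0)² = 12.7, so 13 completers. Then 13/0.85 = 15.3, so 16 randomised per group, or 48 over three arms. The noncentral t gives 14 completers and 17 randomised, or 51 in total. The stated 123 is not reproduced; 123/16 is about 7.7.

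**2. Unstated conventions that might explain 123.** Randomised per group, margin 2.0 and SD 1.8 throughout:

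| Variant | Per group |
|---|---|
| One-sided alpha .0125, 80% power | 20 |
| One-sided alpha .00625, 80% power | 24 |
| Alpha .025, 90% power | 23 |
| Alpha .0125, 90% power | 26 |
| Two one-sided tests for equivalence, alpha .025, 80% power | 22 |
| Same, alpha .0125, 90% power | 30 |
| 80% power within each of the four disorders | 62 to 66 |

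None comes near 123.

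**3. A different SD.** With 104 completers per group, 80% power at margin 2.0 needs a common SD of 2.0 / (2.8016 × √(2/104)) = 5.15. The largest possible SD on a 0–10 scale is 5.0 (half the scores at each end). The paragraph gives 1.8 for the usual care groups only. If the stepped care SD alone differed, it would have to be √[(2.0/2.8016)² × 104 − 1.8²] = 7.05, which is also impossible.

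**4. Power at the planned size.** 123 × 0.85 = 104.6, so about 104 completers. SE = 1.8 × √(2/104) = 0.2496. At margin 2.0 the standardised distance is 2.0/0.2496 = 8.01, and 8.01 − 1.96 = 6.05, so power exceeds 99.99% for each comparison. The chance of failing either comparison is at most the sum of two negligible probabilities, so joint power also exceeds 99.99%. At 1.3, the lower end of the quoted range for the minimally important difference, 1.3/0.2496 − 1.96 = 3.25, which gives about 99.9%.

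**5. What does give 123.** Put 0.7 in place of 2.0: 2 × (2.8016 × 1.8 / 0.7)² = 103.8, so 104 completers; 104/0.85 = 122.4, so 123. Only the distance between true difference and margin enters the formula. Margin 0.7 with difference 0, and margin 2.0 with stepped care truly 1.3 points worse, therefore give the same answer. The match depends on the normal approximation; the noncentral t gives 105 and 124.

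**6. What the choice of threshold does.** The confidence half-width with 104 completers is 1.96 × 0.2496 = 0.49. Noninferiority is declared if the observed deficit plus 0.49 is below the margin:

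- margin 2.0: observed deficit up to 2.0 − 0.49 = about 1.5 points
- margin 0.7: observed deficit up to 0.7 − 0.49 = about 0.2 points

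**The case against.** The best defence is that the article names only one margin, 2.0, gives a reason for it, and plans more than enough participants to test it. Taken at face value the error costs no power. N may have been set on grounds that a condensed article leaves out; a design effect of about 8 would also lead to 123. This stands in part: sample size does not endanger the noninferiority test at 2.0, and whether 2.0 is too lenient is a separate question from the arithmetic. It does not rescue the statement, because the paragraph lists its assumptions and says that they give 80% power. They do not.

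A reader might infer that the trial was really designed on a 0.7-point margin, or on a true difference of 1.3, and that 0.7 should now be written in. The document does not support that. Neither value is stated; 1.3 appears only as the lower end of the range for the minimally important difference, and 0.7 lies below that range. Putting 0.7 in place of 2.0 would change the primary decision rule on a guess.

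A reader might also compute power for meeting both comparisons at 0.7, about 69%, and call the trial underpowered for its joint hypothesis. That figure exists only under the inferred margin. At the stated margin joint power exceeds 99.99%.

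**Conclusion.** Wrong as written. The stated margin, true difference, SD, alpha, power, dropout and N cannot all hold. The inputs call for about 16 (17 with the t distribution) randomised per group, and the planned 123 per group gives power above 99.99% at margin 2.0. This rests on a comparison of two means with a common SD of 1.8 and 15% loss. No unequal SD that is possible on the scale closes the gap, and no stated adjustment does.

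The error does not underpower the trial at 2.0. It leaves unexplained how N was derived, and so whether the printed margin is the one the trial was sized to test. The 0.7 distance shows where to look in the original calculation. It is not a finding about what the sponsor used.

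**What to change.** Retrieve the original calculation and rewrite the paragraph so that margin, assumed true difference, SD, power and N agree. Confirm in writing, before any comparative data are seen, which margin governs the primary conclusion.

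- If 2.0 is kept: replace the 80% with the actual power (above 99.9%) and state the real basis for 123 per group.
- If the trial was sized on a smaller margin or a non-zero true difference: state that value and its rationale.

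No change to N is needed. If 2.0 stands, the cost is one corrected paragraph. If the governing margin turns out to be another value, the correction changes the primary decision rule and needs a dated, justified amendment. The timing is still favourable: 65 of 369 participants were enrolled by September 2025 (Results), and no interim analysis is planned (Data Integrity and Analysis).

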## Discussion

### Principal Findings

We anticipate that the stepped care model will be noninferior to usual medical care and usual rehabilitation care in terms of treatment effectiveness. In addition, we expect this model to reduce health care costs by limiting the use of expensive resources, such as consultations with health care providers and medical investigations. As health care costs for MSKDs continue to rise, implementing a stepped care model—where patient education and self-management advice are prioritized initially, and usual care is reserved for those whose symptoms persist—could improve access to care without compromising quality. This approach also empowers patients to take an active role in managing their condition, overall health, and well-being from the outset.

MSKDs are among the most common reasons for primary care consultations, with up to 20% of adults seeking care for these conditions annually [8], and approximately 30%-40% of individuals with MSKDs reporting contacting their family physician for these complaints [30]. Despite their high prevalence, MSKDs remain difficult to treat effectively beyond the acute phase [96-98]. Given the significant impact of MSKDs on individuals’ activities and participation, as well as their contribution to societal burdens such as work loss, disability pensions, early retirement, and increased demand for social support [3,4], it is crucial to explore innovative care models to address these challenges.

The findings from this study could inform systemic changes in care delivery, improving access to treatment while reducing the average cost per care episode. Ultimately, this study aims to provide robust evidence supporting more efficient, patient-centered care models for a prevalent and costly set of conditions.

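### The 2.0-point noninferiority margin is the top of the protocol's own MCID range (1.3 to 2.0), so losses that part of the range calls important count as noninferior

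*Protocol article*

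**What the plan says.** The sample-size paragraph closes the Population and Sample Size section of the protocol article, after the anterior knee pain criteria. It plans the trial "using a noninferiority margin of 2.0 (out of 10) points on the primary outcome measure". The reason given is: "This margin is based on the highest suggested minimally clinically important difference for the Pain Interference subscale". The section on the primary outcome says of the same subscale: "Its minimally clinically important difference ranges from 1.3 to 2.0 out of 10 points".

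The other planning inputs are "an SD of 1.8 in the usual care groups", "a 1-sided alpha level of .025", 15% dropout at 24 weeks and no true difference: "The sample size calculation assumes a true mean difference of 0 between groups". The stated result is: "With 123 participants per group, we will have 80% power to test the noninferiority of the stepped care model".

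The Introduction frames the primary objective as whether stepped care is as effective as each of the two usual care models. The Introduction and the Discussion both present the model as a way to improve access with no loss of quality.

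**The concern.** A noninferiority margin is the loss that the trial must rule out before it may say that the new approach gives up nothing that matters. Here the protocol has a range of estimates for the smallest difference that matters and takes the largest. Every mean loss from 1.3 to just under 2.0 is then important on part of that range and still inside the margin.

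What is at stake is the primary conclusion. A trial that excludes only losses of 2.0 or more cannot show that stepped care is as effective as usual care, or that quality is kept, if losses of 1.3 or more may matter to patients.

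**Working it through.** **Inputs.** Margin 2.0, SD 1.8, true difference 0, one-sided alpha 0.025, power 80%, dropout 15% and 123 per group, all from the sample-size paragraph. MCID range 1.3 to 2.0, from the primary outcome section. Evaluable per group: 123 × 0.85 = 104.55, taken as 104. Higher scores are worse, so a loss is a positive difference for stepped care. Joint figures for the two comparisons assume a correlation of 0.5, which follows from the shared stepped care arm with equal group sizes.

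**1. The plan's own figure.** n per group = 2 × [SD × (1.960 + 0.842) / (margin − true difference)]².
- Stated inputs: 2 × (1.8 × 2.802 / 2.0)² = 12.7, so 13 evaluable; 13 / 0.85 gives 16 randomized. The stated 123 is not reproduced.
- One-sided alpha from 0.005 to 0.05, power of 90% or 95%, and a two-sided equivalence test never give more than 35 per group.
- A margin-minus-difference of 0.7: 2 × (1.8 × 2.802 / 0.7)² = 103.8, so 104 evaluable; 104 / 0.85 gives 123. This matches exactly. It corresponds to a margin of 0.7 with true difference 0, or to a margin of 2.0 with a true difference of 1.3.

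**2. What passes at a margin of 2.0.** SE = 1.8 × √(2/104) = 0.250. The largest observed loss that still passes is 2.0 − 1.96 × 0.250 = 1.51 points.

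**3. Chance of declaring noninferiority at a true loss t.** P = Φ((2.0 − t)/SE − 1.96).

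| True loss | Per comparison | Both comparisons |
|---|---|---|
| 1.0 | 98% | 96% |
| 1.3 | 80% | 69% |
| 1.5 | 52% | 35% |
| 1.65 | 29% | 15% |
| 1.8 | 12% | 4% |
| 2.0 | 2.5% | 0.5% |

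**4. Sensitivity to the SD.** The source of the SD of 1.8 is not available here, so larger values are assumptions. At a true loss of 1.3 the chance per comparison is 63% for SD 2.2, 52% for SD 2.5 (36% for both) and 39% for SD 3.0. A model that uses the baseline score would lower the residual SD and raise these figures.

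**5. Power with a tighter margin.** True difference 0, 104 evaluable per group; P = Φ(margin/SE − 1.96).

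| Margin | SD 1.8: each / both | SD 2.5 (assumed): each / both |
|---|---|---|
| 2.0 | above 99.9% / above 99.9% | above 99.9% / above 99.9% |
| 1.3 | 99.9% / 99.9% | 96% / 93% |
| 1.0 | 98% / 96% | 82% / 72% |
| 0.7 | 80% / 69% | 52% / 36% |

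**The case against.** The protocol ties its margin to a published MCID and says openly that it took the highest value. Which end of a range of estimates to use is partly a judgement, and the source of the estimates is not available here. That stands, and it is why any new margin needs a clinical rationale as well as a power figure. It does not explain why the most lenient value is right for a claim of equal effectiveness.

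A reader might infer that the trial would probably pass stepped care for any clinically important loss. The figures do not support that. The chance exceeds 50% per comparison only for true losses up to about 1.51, and for both comparisons only up to about 1.41. Toward the top of the MCID range it is small. The probabilities also depend on the SD of 1.8.

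A reader might also infer that an ineffective model could meet the margin, because the article gives no effect of usual care over no care and the Discussion says that "MSKDs remain difficult to treat effectively beyond the acute phase". That remark is general background without an effect size. The preserved-effect argument may sit in a fuller document that is not shown, so the inference is not made here.

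Finally, 2.0 may not be the value that was used for the design. If the sample size was computed with a margin of 0.7, the text contains a reporting error and the probabilities in step 3 would not apply. That is a fair limit, but the document states 2.0, and a trial analysed as written would be judged against 2.0.

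**Conclusion.** The point holds as a defect in the stated margin. On the protocol's own figures, 2.0 is the upper end of the range of differences that may matter, and observed losses up to about 1.51 would be declared noninferior. At a true loss equal to the lower MCID bound, that happens with 80% probability per comparison and 69% for both, given SD 1.8 and 104 completers per group. With an assumed SD of 2.5 it is 52% per comparison. A positive result against 2.0 would not support the claims of equal effectiveness and uncompromised quality.

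The margin is not forced by feasibility at the stated SD. The sample-size statement is also inconsistent with its own inputs, and that has to be settled first because it decides which margin the trial was built on.

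**What to change.** 1. State which margin and which true difference produced 123 per group, and correct the sample-size statement to match. If the margin used was 0.7, correct the 2.0 in the text.
2. If 2.0 was intended, set the primary margin below 1.3, for example 1.0, before any unblinded look, and give a clinical rationale for the value chosen.
3. Report the comparison with 2.0 only as a secondary reading.

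The timing allows this: 65 of 369 participants were enrolled by September 2025, no interim analysis is planned, and the statistician is to stay blinded.

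**Cost.** Changes of wording in the protocol, the analysis plan and the registry entry, and some surplus power. At a margin of 1.0, power at true difference 0 falls from above 99.9% to 98% per comparison (96% for both) with SD 1.8, or to 82% (72% for both) if the SD is 2.5. A margin of 0.7 costs more: 80% per comparison and 69% for both with SD 1.8. No extra participants are needed for a margin of 1.0, but the comfort of that choice depends on the SD.
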